### 2.5. Sample Size and Power

Sample size is justified a priori following current recommendations [70], with all calculations derived analytically from noncentral *F*, t, and chi-square distributions at a two-tailed significance threshold of α = 0.05 and a target power of 1 − β = 0.80, reproducible in G*Power 3.1 (“ANOVA: Repeated measures, within factors”) and consistent with recent tutorials on power analysis for repeated-measures designs [63]. The primary test is a repeated-measures ANOVA (four within-subject levels) on each composite score. Assuming a correlation between repeated measurements of ρ = 0.50 (a typical value for repeated attitudinal ratings, to be verified in the pilot), the minimum sample is 24 participants for medium effects (*f* = 0.25) and 138 for small effects (*f* = 0.10); under the conservative assumption ρ = 0.30, these become 32 and 193, respectively. The minimum analyzable threshold is therefore set at *N* = 140 valid participants, sufficient to detect even small between-scenario effects under realistic conditions. Because these thresholds depend on ρ, an adaptive rule is pre-registered for the case in which the pilot estimate falls outside the assumed ρ = 0.30–0.50 range. The pilot returns $\hat{\rho }$ with a 95% confidence interval, and every threshold is recomputed at its lower bound, ρ_L_, which is the conservative choice. The number of valid participants required to detect *f* = 0.10 at power 0.80 is 274, 247, 220, 193, 165, and 138 for ρ_L_ = 0, 0.10, 0.20, 0.30, 0.40, and 0.50, respectively; an intermediate ρ_L_ is rounded down to the nearest tabulated value, so that the rule is fully determined in advance for any estimate the pilot can return. Two consequences follow. The recruitment target does not change because the requirement is a decreasing function of ρ and reaches only 274 in the theoretical worst case of ρ_L_ = 0; *N* = 300 preserves power ≥0.80 against small between-scenario effects for every value ρ can take, and the target is in any case set by the person-level analyses described below, which do not depend on ρ. The analytic floor does change: it is redefined as the value tabulated above for the observed ρ_L_, so that it remains at the pre-specified *N* = 140—rounded up from 138—only when ρ_L_ ≥ 0.50 and rises to 165, 193, 220, 247, or 274 as ρ_L_ falls to 0.40, 0.30, 0.20, 0.10, or 0. A ρ_L_ below 0.10 would in addition indicate that the composites are unstable across repetitions rather than that participants are inconsistent, and would therefore also trigger re-inspection of pilot reliability and of the measurement-invariance assumptions before the main study is launched. Any application of this rule, and the $\hat{\rho }$ that triggered it, will be recorded in the pre-registration and reported in the results article.

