
The recruitment target is *N* = 300 valid participants. This target is dictated not by the within-subjects effects (for which power at *N* = 300 is 0.99 for small effects at ρ = 0.50, with a minimum detectable effect of *f* = 0.07), but by the person-level analyses: the familiarity moderation (minimum detectable interaction *f*^2^ = 0.037 at *N* = 300), the global preference test (minimum detectable *w* = 0.21 on 5 degrees of freedom), and descriptive analyses of demographic subgroups. A small interaction effect (*f*^2^ = 0.02) would require *N* ≈ 550; H4 therefore remains partially exploratory, and a non-significant result will not be interpreted as evidence of absence. At *N* = 300, dependent pairwise comparisons detect differences from *dz* = 0.16 (uncorrected) and *dz* = 0.20 (at the Bonferroni bound for six pairwise comparisons), so all six scenario contrasts can be treated as confirmatory. Counterbalancing entails no loss of sensitivity for the primary comparisons: with sequence entered as a four-level between-subjects factor, the autonomy main effect retains 3 degrees of freedom and the same noncentrality, so the minimum detectable effect at *N* = 300 remains *f* = 0.07. The scenario × sequence interaction—the direct test of order dependence—carries 9 degrees of freedom and a minimum detectable effect of *f* = 0.08 at ρ = 0.50 (*f* = 0.10 at ρ = 0.30), giving power of 0.95 against a small order effect of *f* = 0.10; the serial-position main effect in the additive model carries 3 degrees of freedom and matches the sensitivity of the autonomy effect itself. Order artifacts large enough to masquerade as the hypothesized autonomy gradient are therefore detectable, rather than being assumed away. In the pilot, by contrast, the ascending and descending arms (*n* = 25 each) bound order effects only at *f* = 0.17, which excludes medium-to-large artifacts but not small ones; the definitive test is the main-study interaction. Table 2 summarizes the power analysis, and Figure 1 shows achieved power as a function of the number of valid responses.

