
### 2.9. Statistical Analysis

#### 2.9.1. Primary Analyses

Each composite score (acceptability, trust, perceived risk) will be analyzed by a mixed repeated-measures ANOVA, with autonomy level (four scenarios) as the within-subjects factor and presentation sequence (four Williams sequences) as the between-subjects factor. The Greenhouse–Geisser correction will be applied when Mauchly’s test indicates a sphericity violation (Huynh–Feldt for ε between 0.75 and 1), and the multivariate approach (Pillai’s criterion) will be reported in parallel as a sphericity-robust check. H1 and H2 will be tested with within-subjects trend contrasts across the autonomy gradient. Because acceptance need not fall in a straight line, the complete set of orthogonal polynomial contrasts—linear, quadratic, and cubic—is pre-specified, and each is reported together with the proportion of the omnibus effect it accounts for. A purely linear profile leaves the quadratic and cubic components negligible, whereas a step between two adjacent levels appears as a large linear component accompanied by a substantial quadratic or cubic one. Because every monotone step is linear-dominant, the polynomial decomposition establishes departure from a straight line but cannot by itself locate the break; the break is identified only from the Holm-corrected adjacent-pair contrasts (A–B, B–C, C–D). A quadratic-dominant profile with a small linear component would instead indicate a non-monotone pattern, which the hypotheses do not predict and which would be reported as such. A non-monotonic or threshold pattern will be reported as such rather than summarized by the linear trend alone. Post hoc comparisons use dependent-samples *t*-tests for the six scenario pairs with Holm’s sequential correction, applied within each hypothesis-defined family of tests in line with current guidance on multiplicity control [74]. Effect sizes will be reported as partial η^2^ for omnibus tests and Cohen’s dz for pairwise comparisons, with 95% confidence intervals, following effect-size-centered reporting recommendations [64]. Assumption checks include graphical inspection of difference-score distributions; as a distributional robustness analysis, the Friedman test with Holm-corrected Wilcoxon signed-rank pairwise comparisons will be reported alongside each primary test—supplemented by ordinal (cumulative-link) models as sensitivity analyses for the Likert-based outcomes [71]—and the concordance of parametric and nonparametric conclusions stated explicitly. Order dependence is tested directly as the scenario × sequence interaction; a non-significant interaction, together with equivalence of the four sequence-specific profiles, supports pooling across sequences. Independently of that test, the autonomy effect is re-estimated from a linear mixed model with random intercepts per participant and additive fixed effects of autonomy level and serial position (1–4). The Williams square renders this model identified, so the estimate is adjusted for arbitrary—not merely linear—serial-position and fatigue effects, while first-order carry-over is balanced by the design rather than modeled; position-adjusted and unadjusted estimates are reported side by side, and any material divergence between them is treated as evidence of an order artifact and interpreted accordingly. Perceived difficulty (DIF1) and perceived technical sophistication (MAN2) are each added as time-varying covariates in further sensitivity models, addressing fatigue and the possibility that responses track the apparent complexity of the system rather than its autonomy. Finally, between-person heterogeneity in response profiles is examined by adding a random slope for the linear autonomy contrast and testing the improvement in fit by a likelihood-ratio test; a substantial random-slope variance indicates that an average trajectory conceals distinct response patterns and licenses the exploratory typology described in Section 2.9.2. Because a non-significant test is not evidence of absence, a smallest effect size of interest of *dz* = 0.20—the value detectable at the Bonferroni bound for the six pairwise contrasts at *N* = 300—is fixed in advance, and equivalence testing by two one-sided tests against that bound is reported alongside every null pairwise result, so that any claim that two adjacent scenarios do not differ rests on an equivalence test rather than on the absence of significance.

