
#### 2.9.2. Secondary and Exploratory Analyses

(i) Moderation (H4): the scenario × AI familiarity (B1, centered) interaction, via repeated-measures ANCOVA or a linear mixed model with random intercepts per participant, the recommended framework for vignette data [62]; presentation sequence is retained as a between-subjects factor here, as in every repeated-measures model in this protocol. (ii) Person-level multiple regression: mean acceptability across scenarios predicted by AI familiarity, general AI attitudes, and demographics (reporting *B*, *SE*, β, 95% CI, R^2^, VIF). (iii) Responsibility migration (H3): a 4 × 4 mixed ANOVA (scenario × actor, RES1–RES4, both within-subjects; presentation sequence between-subjects) with Greenhouse–Geisser correction; the scenario × actor interaction is the direct test of H3. Because H3 is confirmatory, it receives the same order controls as H1 and H2: the sequence terms are inspected first, and the migration estimate is repeated in a linear mixed model containing an additive serial-position term. (iv) Responsibility concentration: a normalized Herfindahl–Hirschman index computed per scenario from the relative weights of the three responsible actors (surgeon, hospital, AI developer; RES4—unavoidable medical uncertainty—is not a responsible actor and is analyzed separately), compared across scenarios by mixed repeated-measures ANOVA with sequence as a between-subjects factor; low values index diffusion of responsibility across actors, operationalizing the “problem of many hands” described in the responsibility literature [44,45]. (v) RES5 (moral duty) and RES6 (outcome-independent accountability): mixed repeated-measures ANOVAs across scenarios with sequence as a between-subjects factor, Holm-corrected within the family. (vi) Global preference (P1): a goodness-of-fit chi-square with standardized residuals over six analysis categories on 5 degrees of freedom. The six categories are the four scenarios, “I would prefer AI not to be involved in any way,” and a combined “no clear preference” category; the last pools the item’s two undecided options (“I have no preference” and “I cannot decide”), which are combined a priori because neither expresses a preference between scenarios and each is expected to be sparse. Consistency between stated preference and each participant’s maximum-acceptability scenario is reported descriptively. (vii) Exploratory: P4a and P4b (the surgeon’s permanent legal and, separately, moral responsibility) analyzed descriptively, compared with each other by a dependent-samples test on the within-person difference, and correlated with RES5/RES6; free-text concerns (P2) summarized by brief thematic analysis. (viii) Sensitivity analyses: primary analyses repeated (a) excluding participants with a single attention-check failure (who are retained under the primary rule) and (b) excluding participants with any comprehension failure, to demonstrate that conclusions do not depend on the cleaning criteria [69]. (ix) Order effects: descriptive profiles by sequence, the scenario × sequence interaction with its effect size and 95% confidence interval, and sequence-specific manipulation-check profiles. (x) Response-pattern typology (exploratory): where the random-slope test of Section 2.9.1 indicates heterogeneity, individual acceptability trajectories across autonomy levels are classified by latent-class growth analysis, with class enumeration by BIC and entropy and a minimum class size of 5% fixed in advance, and class membership described against AI familiarity, healthcare-system trust, and demographics; no inferential claim is attached to this analysis. (xi) Healthcare-system trust (B6) enters the person-level regression of (ii) as a covariate and is examined as an exploratory moderator of the autonomy effect, alongside healthcare contact frequency (B5) and prior surgical experience (B4, B4a). (xii) Subgroup analyses, all of which are secondary or exploratory, are governed by a minimum-cell rule fixed in advance: inferential tests within a subgroup are reported only where that subgroup contains at least 50 valid participants, the size at which a within-subject difference in *dz* = 0.40 is detectable at power 0.80; subgroups of 30–49 are reported descriptively with 95% confidence intervals and labeled as underpowered; subgroups below 30 are pooled into a residual category or not reported. A difference between subgroups is never inferred from a significant effect in one and a non-significant effect in another; only the formal interaction term, with its own confidence interval, supports such a claim. The set of moderators is fixed a priori, in the pre-registration, to seven: AI familiarity (B1), healthcare-system trust (B6), healthcare contact frequency (B5), prior surgical experience (B4/B4a), education (D3), age (D2), and field of activity (D4). Results are reported for all seven irrespective of significance, and no further moderator is added after the data are seen. (xiii) Missing data: because all closed items are mandatory, missingness in the dependent variables is structurally impossible within a submitted questionnaire. Two other forms of missingness remain. The first is unit-level, from questionnaires abandoned before submission. The platform is configured not to store partial submissions, so responses from abandoned questionnaires are neither retained nor analyzed (Section 2.10 and Appendix A.1). Attrition is therefore characterized from the platform’s page-level counters—how many participants reached each page—rather than from partial response data, and is reported as drop-out by serial position in the participant-flow diagram. Analyses are accordingly restricted to complete cases, that is, participants with all four scenario blocks, and no imputation is performed: with no partial records retained, there are no incomplete cases to impute. The second is item-level, on the background and demographic items that offer a “prefer not to answer” option or, in the case of B4 and B4a, are not displayed where the explicit health-data consent is declined; these are treated as a distinct category descriptively and as missing in inferential models, with a sensitivity analysis retaining the category in the person-level regression. Because complete-case analysis is not neutral when attrition is differential, drop-out is compared across the four presentation sequences, and any imbalance is reported and carried into the interpretation of the order analyses. All tests are two-tailed at α = 0.05, with exact *p*-values, effect sizes, and 95% confidence intervals reported for all tests, including non-significant ones. On closed 1–7 scales, no distribution-based outlier removal is applied.

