## 3. Expected Results

Based on the algorithm-aversion and trust studies [19,37,38], we expect acceptability and trust to decline—and perceived risk to rise—across the autonomy gradient from Scenario A to Scenario D, with the largest drop anticipated at the transition to autonomous planning (Scenario D), where the surgeon’s corrective role is described as residual. Whether that decline is a gradient or a step is an open question that the design is equipped to address: a step would show as a substantial quadratic or cubic component alongside the linear one, and its location would be identified by the adjacent-pair contrasts, which we expect to place the largest single drop at C–D. Nor do we assume the pattern is homogeneous across participants; a substantial random-slope variance would itself be informative, indicating that an average trajectory conceals distinct groups of respondents rather than describing a shared response. The expectation of decline is, in any case, consistent with survey evidence that public comfort is conditional on physician supervision [24,25,31]. For responsibility attribution, we expect the surgeon to be assigned the dominant share in low-autonomy scenarios [41], with a progressive migration toward the AI developer—and possibly a diffusion of responsibility across actors, indexed by falling Herfindahl concentration—as autonomy increases [44,45]. We expect the manipulation check (perceived AI control) to order the scenarios from A to D within each of the four presentation sequences, validating the experimental gradient independently of serial position, and we expect no scenario × sequence interaction. Should one nevertheless appear, the position-adjusted mixed-model estimate becomes the primary basis for interpreting H1–H3, and the magnitude of the order effect will itself be reported as a finding about the stability of vignette-based autonomy judgments. Given the design’s sensitivity (power of 0.99 against small within-subjects effects at ρ = 0.50, and 0.95 at ρ = 0.30, for the target sample), a null result for a primary hypothesis would place a tight upper bound on the size of any autonomy effect rather than leaving the question open; the pre-specified equivalence tests of Section 2.9.1 make that bound explicit rather than infer absence from non-significance [70]. The moderation hypothesis (H4) is powered only for medium-small interactions and will be interpreted with corresponding caution. Results will inform the ordering of public concerns along the assistance-to-autonomy continuum and identify which implementation configurations are publicly acceptable entry points for surgical AI in Romania.

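### Random-slope variance is read as showing distinct groups of respondents, and the latent-class step that follows almost never returns a single population

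*Protocol article*

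**What the plan says.** The protocol goes from test to typology in three steps.

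- **The test (Section 2.9.1).** Heterogeneity is examined by "adding a random slope for the linear autonomy contrast and testing the improvement in fit by a likelihood-ratio test". The meaning given to the result is that "a substantial random-slope variance indicates that an average trajectory conceals distinct response patterns and licenses the exploratory typology".
- **The typology (Section 2.9.2(x)).** It runs only "where the random-slope test of Section 2.9.1 indicates heterogeneity". Then "individual acceptability trajectories across autonomy levels are classified by latent-class growth analysis, with class enumeration by BIC and entropy", with a minimum class size of 5%. Classes are described against AI familiarity, healthcare-system trust and demographics, and the section disclaims any inferential claim.
- **The reading (Section 3).** Substantial slope variance would be informative, "indicating that an average trajectory conceals distinct groups of respondents rather than describing a shared response".

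No entropy cut-off, one-class comparator or within-class variance is stated. Section 2.12 and Table 5 label the analysis exploratory.

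**The concern.** The question asked is whether respondents fall into distinct groups. The likelihood-ratio test answers another: whether slopes vary at all, given a random intercept and equal residual variance. Ordinary continuous variation in slopes rejects that null without any groups. So can a common shift for everyone, if the spread differs between scenarios or scores pile up at 7.

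The second stage does not correct the first. By its standard definition, latent-class growth analysis gives everyone in a class the same trajectory plus independent error. Stable differences between people in overall level can then be absorbed only by adding classes.

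At stake is a descriptive set of respondent types that may be slices of a continuum, profiled against familiarity and trust, together with a statement about groups that the test cannot support.

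**Working it through.** **Inputs from the protocol.** N: "The recruitment target is *N* = 300 valid participants" (Section 2.5). Correlation: "Assuming a correlation between repeated measurements of ρ = 0.50", with 0.30 as the conservative value (Section 2.5). Level: "All tests are two-tailed at α = 0.05" (Section 2.9.2). Minimum class 5%.

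**Inputs assumed.** The protocol gives none of these: outcome SD 1.4; scenario means 5.2, 4.8, 4.6, 3.4; slope SD 0, 0.15, 0.3 or 0.5 points per level.

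**Step 1: the plan's own figures.** It states no operating figure for the typology, so only the design inputs can be checked. With λ = N·m·f²/(1−ρ), m = 4 and f = 0.10:

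- ρ = 0.50: λ = 300·4·0.01/0.50 = 24, power 0.991 (stated 0.99).
- ρ = 0.30: λ = 12/0.70 = 17.1, power 0.949 (stated 0.95).

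The required N of 274, 247, 220, 193, 165 and 138 for ρ = 0 to 0.50 also reproduces.

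**Step 2: why one class cannot win.** A one-class latent-class growth model implies zero correlation between scenarios. Under the plan's ρ = 0.50, the correlation matrix has determinant (1−ρ)³(1+3ρ) = 0.125 × 2.5 = 0.3125. The expected deviance that the one-class model forgoes is therefore 300 × (−ln 0.3125) = 300 × 1.163 ≈ 349. At ρ = 0.30 the determinant is 0.343 × 1.9 = 0.652, giving 300 × 0.428 ≈ 128. An extra class with a linear trajectory costs three parameters, so 3 × ln 300 = 17.1 BIC points. Even a crude discrete approximation to the intercept distribution repays that.

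**Step 3: simulation from one normal population.** Samples have a random intercept and a normal random slope, with no classes. The gate is the likelihood-ratio test on 2 df at 0.05. Latent-class growth models were fitted by EM with K = 1 to 5, and K was chosen by BIC among solutions with every class at least 5%.

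| Slope SD | ρ | Variant | Samples | Gate opens | K ≥ 2 | Both |
|---|---|---|---|---|---|---|
| 0 | 0.50 | linear | 100; 150 | 0.05; 0.04 | 1.00 | 0.05; 0.04 |
| 0.15 | 0.50 | linear | 150 | 0.17 | 1.00 | 0.17 |
| 0.3 | 0.50 | linear | 100 | 0.94 | 1.00 | 0.94 |
| 0.3 | 0.50 | quadratic | 150 | 0.91 | 1.00 | 0.91 |
| 0.3 | 0.50 | 1–7 items | 150 | 0.70 | 1.00 | 0.70 |
| 0.3 | 0.30 | linear | 150 | 0.71 | 1.00 | 0.71 |
| 0.5 | 0.50 | linear | 100 | 1.00 | 1.00 | 1.00 |

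Two or more classes were chosen in all 1050 samples, usually three. Further runs put the joint rate at about 2–5% for slope SD 0 and 17–20% for slope SD 0.15.

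**Step 4: the same latent shift for everyone, with unequal spread or a ceiling.**

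- Residual SD rising from 0.50 to 0.95 across A–D: the gate opened in 85% to 94% of samples in separate runs. With scenario-specific residual variances, the 85% fell to 9%.
- Items rounded and capped at 7: 68–75% with the mean for A near 5.8, and 96% with it at 5.9. Scenario-specific variances lowered the 96% only to 66%.

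Where classes were also fitted under these two conditions (40 to 100 samples per setting), two or more were chosen every time.

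**Step 5: entropy.** Relative entropy divides by N·ln K, which is zero at K = 1, so without a cut-off it cannot favour one class. The false solutions had median entropy 0.53 to 0.71. If a cut-off of 0.80 were imposed (an assumption), at most 2% of samples kept two or more classes.

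**Step 6: is the method the cause?** A mixture keeping a random intercept and slope within class, fitted to one-population data with slope SD 0.3, preferred two classes in 0 of 40 samples. With random intercepts only, continuous slopes, a ceiling, or unequal variances, the chosen latent-class solution beat the one-class random-slope model on BIC in 0–1% of samples.

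**The case against.** The strongest reply is that the plan limits the damage itself. The typology is gated, exploratory and free of inferential claims, and Section 2.12 bars hypothesis-testing language for it. Table 5 also reports the random-slope SD, so the size of the variation is visible beside its p-value. All of this stands, and it keeps the point small.

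A reader might infer that a typology will be reported whether or not one exists. The documents do not support that. Section 2.9.2(x) makes the analysis conditional on the slope test, and with parallel, equally variable responses that test opens the gate in only about one study in twenty. The 100% figure applies to class selection once the gate is open. Nor does the protocol treat slope variance as proof: Section 2.9.1 speaks of what it indicates, and Section 3 is conditional. Section 3 is also right that, under varying slopes, the average is not a shared response.

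It can also be said that an entropy cut-off, the comparator models and the within-class variances belong in the fuller analysis plan. That is fair for the cut-off, and a conventional one would screen out most false solutions. It does not answer the main point, because the reading of slope variance and the choice of method are both stated in the text. The exploratory label covers the classification, whereas the two sentences attach their meaning to the slope variance before any classification is run.

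**Conclusion.** The point holds in limited form and is minor. Slope variance is evidence of between-person variation in the autonomy gradient, not of distinct groups, and Sections 2.9.1 and 3 read it as the latter. When the gate opens, the stated class selection finds two or more classes in essentially every one-population sample at N = 300.

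The chance of a false typology is about 2–5% with no slope variance and equal residual variances, 17–20% at slope SD 0.15, and roughly 70–95% at slope SD 0.3 or under plausible unequal variances or a ceiling. It reaches 100% at slope SD 0.5. A ceiling is plausible because Section 3 expects acceptability to be highest at A, on a closed 1–7 scale.

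These rates rest on assumed slope SDs, outcome SD, residual SDs and means, on latent-class growth analysis in its standard form, and on entropy being used without a cut-off. The tests of H1–H3 are untouched. The harm is a misleading exploratory typology and one unsupported statement about groups.

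**What to change.** Before pre-registration:

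1. In Sections 2.9.1 and 3, say that random-slope variance shows between-person variation in the autonomy gradient, and drop the inference to distinct patterns or groups.
2. In Section 2.9.2(x), add the one-class random-intercept and the one-class random-intercept-and-slope models to the BIC comparison. Allow a random intercept within class in the mixtures. Report a typology only if a multi-class model beats the one-class random-slope model on BIC.
3. As a useful addition, fit the slope test with scenario-specific residual variances. This helps with unequal spread but does not by itself cure a ceiling (Step 4).

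In simulation the rule in item 2 reported classes in 0% of samples with random intercepts only or with continuous slopes, and in about 13% under the ceiling. It found them in 100% when two real classes existed. That last figure comes from one favourable case: 70% of respondents nearly flat and 30% with a steep drop at D.

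The cost is some wording and a few more model fits. A typology will be reported less often, and some false classes will remain under a strong ceiling. No data have been collected, so nothing already done is lost.
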